### Research Aim C)

We will study prescribing and its relationship with multimorbidity clusters, and we anticipate focusing on the clusters under study in Research Aim B). We will investigate continuous prescriptions, defined as a prescription from within the same class repeated up to 3 times per year (allowing for drug switching between classes, and stockpiling between prescriptions). This will allow us to define polypharmacy, using the commonly used definition (the simultaneous, continuous prescription of 5 or more medications) but also to develop our own characterisation of the association between prescribing patterns and multimorbidity, e.g. the role of specific drugs. We will use several methodologies spanning machine learning and artificial intelligence which have not yet been used commonly in this field. The methods we expect to use overlap (in part) with our clustering approaches, and include: Association Rule Mining (ARM), or market-basket analysis; Latent Class Analysis (LCA), traditional iterative clustering methods (k-means, Hierarchical Cluster Analysis), as well as matrix factorisation methods. We will initially focus on ARM and factorisation methods, which are complementary and have proved successful in recent multimorbidity studies.

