##### (c) Prescribing

- Continuous prescriptions: drugs within the same class prescribed 3 times or more per year: name, class and date of prescription.
- Polypharmacy: we will construct a derived variable, and expect to define this as the simultaneous use of five or more continuous prescriptions.

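### Protocol Sections M and N set the 'continuous prescription' threshold in opposite directions, so the Aim C polypharmacy variable depends on which section is followed

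*Protocol*

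**What the plan says.** Section M, under primary exposures, (c) Prescribing, gives the rule "Continuous prescriptions: drugs within the same class prescribed 3 times or more per year". For polypharmacy the authors "expect to define this as the simultaneous use of five or more continuous prescriptions".

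Section N, Research Aim C, gives the term a second definition: "defined as a prescription from within the same class repeated up to 3 times per year", with the qualifier "allowing for drug switching between classes, and stockpiling between prescriptions". The next sentence ties polypharmacy to it: "This will allow us to define polypharmacy, using the commonly used definition", which is then spelled out as "the simultaneous, continuous prescription of 5 or more medications".

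The threshold of five is the same in both places. The rule for what may be counted towards the five is not. Nothing else in the protocol reconciles the two, and the only amendment shown concerns the Pregnancy Register.

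**The concern.** Section M sets a lower bound of three and Section N an upper bound of three, for one named variable. Someone deriving the exposure would look first to the analysis section. Coded as written, that section drops drugs issued most regularly and keeps those issued rarely.

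The variable matters to the study. Polypharmacy is listed among the primary exposures in Section M, is named as an outcome of the cohort analysis in Section G, and is the subject of Aim C. The findings are also to be validated in Aurum after code mapping. Two analysts could each follow the protocol and build variables that disagree for most prescribing frequencies.

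**Working it through.** The protocol gives no sample size, power or event figure that rests on this definition, so there is no stated figure to reproduce. The check compares the two rules.

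**Inputs.** Let k be the number of issues of one drug class in a year.

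- Section M: continuous if k ≥ 3.
- Section N, reading A (the ceiling counts issues): continuous if k ≤ 3.
- Section N, reading B (the ceiling counts repeats after a first issue): repeats = k − 1, and 1 ≤ k − 1 ≤ 3 gives 2 ≤ k ≤ 4.
- Both sections: polypharmacy if at least 5 continuous drugs are held at the same time.

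**Step 1: one drug class, k from 1 to 13.**

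| Issues per year | Section M | Section N, reading A | Section N, reading B |
|---|---|---|---|
| 1 | no | yes* | no |
| 2 | no | yes | yes |
| 3 | yes | yes | yes |
| 4 | yes | no | yes |
| 5 to 13 | yes | no | no |

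*Only if the requirement that the prescription be repeated is ignored.

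The counts that qualify under both sections are {3} on reading A and {3, 4} on reading B. Section M alone accepts 4 and above on reading A, and 5 and above on reading B.

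**Step 2: a patient holding five drug classes at the same time.**

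| Issues per class per year | Section M | Section N, reading A | Section N, reading B |
|---|---|---|---|
| 12 (monthly) | 5 continuous: polypharmacy | 0: none | 0: none |
| 6 (two-monthly) | 5: polypharmacy | 0: none | 0: none |
| 4 | 5: polypharmacy | 0: none | 5: polypharmacy |
| 3 | 5: polypharmacy | 5: polypharmacy | 5: polypharmacy |
| 2 | 0: none | 5: polypharmacy | 5: polypharmacy |

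The monthly and two-monthly rows do not depend on how Section N is read. The row with two issues assumes that use of the five classes overlaps in time, as both definitions of polypharmacy require.

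**Step 3: which rule fits the rest of the protocol.** Section T reasons that people who get repeat prescriptions can, to some extent, be taken to use their medicines regularly. It sets aside over-the-counter and in-hospital drugs because such use is usually brief and so matters less for polypharmacy. That reasoning fits a minimum number of issues. It does not fit a ceiling that removes monthly repeats.

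**The case against.** The strongest reply is that Section N contains a plain wording slip. The term being defined is continuous use, Section M states a clear minimum, and Section T supports it, so few analysts would code a ceiling. The study is descriptive and hypothesis-generating, the outcomes listed in Section C do not use this variable, and Section M presents its polypharmacy definition as provisional. This lowers the likely harm. It does not remove the contradiction: the protocol nowhere says that the ceiling is a slip, and the tentative wording in Section M covers the five-drug rule, not the three-issue rule.

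A reader might infer more than the text supports:

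- *A single short course counts as continuous under Section N.* That ignores the requirement that the prescription be repeated. A class issued once does not qualify on reading B, and qualifies on reading A only if that word is set aside.
- *Several one-off courses add up to polypharmacy.* Both sections require simultaneous use, so courses scattered over a year do not meet the definition merely by being counted.
- *The rules agree only at exactly three issues.* This holds on reading A; on reading B they also agree at four.
- *The association studied in Aim C would be reversed.* The protocol gives no distribution of prescription frequency, so neither the direction nor the size of any bias can be derived.
- *The switching clause defeats the same-class rule.* The clause can be read as the reason for a low threshold, since a patient who changes class has fewer issues in each. It is an ambiguity, not a shown error.

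**Conclusion.** The contradiction stands, and Section N is wrong as written. The same term has a minimum of three in one section and a maximum of three in the other, with agreement at three issues a year, or at three and four on the more generous reading. On both readings Section N excludes monthly and two-monthly prescribing, so five long-term drugs issued at either interval count as five in Section M and as none in Section N.

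This conclusion needs only the two definitions and the shared threshold of five. How many patients would change category, and what that would do to the Aim C results, is unknown. The text should be corrected before the exposure is derived.

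**What to change.** In Section N, Research Aim C, replace the ceiling with the Section M rule, "drugs within the same class prescribed 3 times or more per year". Derive polypharmacy from that one variable, with the same rule applied in GOLD and in Aurum.

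In the same edit, state how a switch between classes counts towards the same-class threshold, for example whether issues before and after a switch are added together or counted separately by class.

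The cost is one sentence in Section N, a short clarification of the switching clause and one derivation rule. The sample size in Section I and the clustering in Aim A are unaffected.

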### O. Plan for addressing confounding

To address confounding we selected a priori confounders that according to the literature are associated with an increased risk for multimorbidity. The main strategy to address confounding will be the analysis stratification according to sex, age group and ethnic groups (White, Black African and Caribbean, and south Asian).

### P. Plans for addressing missing data

We will assume that the individuals who do not have any recorded code do not have the disease (for further discussion, please also see Section T. Limitations on the study design). We will include patients who have complete data for the stratification variables (e.g. sex, age and ethnic groups) and who have linked measures of deprivation. Given the high levels of missingness for some covariates, i.e. body mass index, total cholesterol, and alcohol intake specific statistical techniques will be applied to handle missing-not-at-random data, e.g. sensitivity analysis and multiple imputation techniques where appropriate.

The design of the study assumes that patients who do not meet the criteria according to the coding algorithm do not have the disease. This may introduce biases due to under-reporting or misreporting. Please see section O for further details.

In the main analyses, where patients will be stratified by age and sex, any individuals with missing data for either will be excluded. In addition, patients without data for ethnicity and deprivation will be excluded from sensitivity analyses.

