#### J. Planned use of linked data (if applicable):

This study will use individual level anonymised data within linked primary and secondary care records. The use of linked data from the NHS Hospital Episode Statistics (HES) for admitted-patient care will allow us to identify hospital-

[figure not shown]

coded conditions that contribute to multimorbidity, to characterise pregnancies, and to add information on health service utilisation, such as number of hospital admissions per year, and to obtain a higher completeness of ethnicity data (a core variable to our study). Moreover, the use of HES data will enable us to undertake validation of diagnosis across primary and secondary care (e.g. HIV and cancer). The linkage to the Office for National Statistics Death registries will allow us to know the cause of death and therefore understand the most common cause of death according to the patterns of diseases' clusters.

Linked area-based measures of deprivation will include the Indices of Multiple Deprivation (IMD) for both patient and practice level. The IMD is an estimate of socioeconomic status that play an important role to multimorbidity. We will use patient level IMD where available. For patients without linked patient level IMD, we will use practice level IMD as a proxy.

We expect that the identification of specific multimorbidity clusters and their different trajectories across ethnic groups will help identify groups of patients who may share similar prognosis and health care needs. Our study findings will support clinicians in the stratification of clinical care and will contribute to preventive strategies across multimorbid conditions. We expect that our study outputs may help improve patient care either directly, e.g. by recognising a common cluster of multimorbidity linked to a specific disease, or indirectly providing scientific support to the inclusion of multimorbidity in clinical practice guidelines and public health policies.

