## N. Data/ Statistical Analysis

### Research Aim A)

We will estimate the prevalence of each condition included in our consensus-built list of 220 conditions across sex, age groups and ethnic groups (White, Black African and Caribbean, and south Asian). We will also describe the presence of multimorbidity ( $\geq 2$  conditions) across different sociodemographic characteristics (age, sex, ethnic groups and deprivation level).

We intend to apply unsupervised machine learning techniques to identify clusters of multimorbidity across an unselected population, and within specific ethnic groups. Recent research suggests that unsupervised learning techniques have potential to identify novel patterns and relationships from electronic health records and reveal latent disease clusters and patient subgroups (16). We will potentially use the overlapping technique, which allows each disease to belong to two or more clusters that present separate degrees of membership. The advantage of using this type of clustering is that the diseases on the boundaries between several clusters are not forced to fully belong to a single cluster, but rather are assigned membership degrees between 0 and 1 indicating their partial membership (17,18). We may apply a prevalence-based revision of the conditions included in our multimorbidity clusters (as used by Kuan and colleagues (2) who set a prevalence cut off of 0.01% in their data-driven analysis) if there is concern that very low prevalence conditions are subject to reporting bias or poor data quality.

We will describe the patterns of multimorbidity by calculating the frequencies and percentages of conditions within each cluster, and diseases will be assigned to the cluster in which they present the highest membership value. The membership value will be estimated using the ratio between the disease prevalence within the cluster by the disease prevalence in the overall population (19). We will examine how clustering varies in the context of more prevalent conditions (e.g. diabetes, hypertension, depression) compared to less prevalent conditions (e.g. HIV and cancer).

We will use the CPRD Aurum as a validation data set, aiming to replicate our methods and validate our findings in an ethnically-diverse East London population.

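### Section P gives two incompatible rules for people with missing ethnicity, so the population for the overall prevalence and clustering is not fixed

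*Protocol*

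**What the plan says.** Section P (missing data) holds both rules.

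- First paragraph: "We will include patients who have complete data for the stratification variables (e.g. sex, age and ethnic groups"), "and who have linked measures of deprivation". This is worded as a condition of inclusion and is not limited to any one analysis.
- Last paragraph: "In the main analyses, where patients will be stratified by age and sex, any individuals with missing data for either will be excluded". The next sentence adds that "patients without data for ethnicity and deprivation will be excluded from sensitivity analyses".

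Four other places bear on the point.

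- Section N, Research Aim A, plans to "identify clusters of multimorbidity across an unselected population, and within specific ethnic groups". These are two separate analyses.
- Section O gives as the main strategy against confounding the "analysis stratification according to sex, age group and ethnic groups", so ethnic group is a stratifier there. The last paragraph of Section P names only age and sex.
- Section J gives as one reason for requesting hospital admission data "to obtain a higher completeness of ethnicity data (a core variable to our study").
- Section J also says of deprivation: "For patients without linked patient level IMD, we will use practice level IMD as a proxy".

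Section C lists the multimorbidity clusters as a primary outcome. Section K defines the study population without mentioning ethnicity.

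**The concern.** A missing-data section should let two analysts arrive at the same dataset, and this one does not. One analyst, following the first paragraph, would drop everyone without recorded ethnicity before any analysis. Another, following the last paragraph, would keep them in the overall prevalence and clustering and drop them only in sensitivity analyses. Ethnicity is a variable whose completeness the protocol itself regards as a problem, so the two datasets may differ by more than a handful of people.

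The choice may also matter for content. A person who has been admitted to hospital has a second chance to have ethnicity recorded, and a person never admitted does not. If ethnicity is required for entry, the retained population may lean towards people who use hospitals. Overall multimorbidity prevalence, and possibly the clusters, could then reflect that selection. Clustering within ethnic groups needs recorded ethnicity in any case. The overall clustering does not, because it is run on conditions.

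**Working it through.** **1. Can the two rules be read together?**

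| | Missing age or sex | Missing ethnicity |
|---|---|---|
| Section P, first paragraph | not included | not included |
| Section P, last paragraph, main analyses | excluded | not named as excluded |
| Section P, last paragraph, sensitivity analyses | – | excluded |

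The last paragraph does not use the word 'only', but it is the natural reading: its main-analysis sentence names age and sex and nothing else, and ethnicity first appears under sensitivity analyses. If the first paragraph applied throughout, the sensitivity exclusion would have nobody to remove. Section O does not settle the matter, since it treats ethnic group as a main stratifier but does not say what happens to people without one. Sections K and N do not settle it either.

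**2. The plan's own figures.** Section I uses Z = 1.96, P = 0.272 and d = 0.002:

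n = 1.96² × 0.272 × 0.728 / 0.002² = 190,174.6, which matches the stated 190,174.

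The allowance for 10% missing data is 190,174 × 1.10 = 209,191.4, which matches the stated 209,191. Neither figure depends on which Section P rule applies.

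**3. What the complete-ethnicity rule could do to overall prevalence.** Let m be the share lacking ethnicity, P the overall prevalence and p the prevalence among those lacking it. Prevalence among those retained is (P − m·p)/(1 − m), so

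bias = m(P − p)/(1 − m).

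The protocol gives neither m nor p, so both are assumptions here. The 10% in Section I is an allowance for unspecified missing data, not an ethnicity figure. I use it only as a starting value.

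Bias in percentage points:

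| P − p (points) | m = 10% | m = 20% | m = 30% |
|---|---|---|---|
| 0 | 0 | 0 | 0 |
| 1.8 | 0.20 | 0.45 | 0.77 |
| 5 | 0.56 | 1.25 | 2.14 |

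Setting the bias equal to the plan's margin d = 0.2 points gives the gap at which it matters by the plan's own yardstick: P − p = 0.2(1 − m)/m.

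- m = 10%: 0.2 × 0.9/0.1 = 1.8 points
- m = 20%: 0.2 × 0.8/0.2 = 0.8 points
- m = 30%: 0.2 × 0.7/0.3 = 0.47 points

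These thresholds do not depend on the value taken for P.

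**4. The same question in terms of completeness.** Let c1 and c0 be ethnicity completeness in people with and without multimorbidity. Prevalence among those retained is P·c1/(P·c1 + (1 − P)·c0), with P = 0.272.

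- c1 = c0 = 0.90: 27.2%, no bias.
- c1 = 0.95, c0 = 0.94: 0.2584/(0.2584 + 0.6843) = 27.4%, about +0.2 points.
- c1 = 0.95, c0 = 0.85: 0.2584/(0.2584 + 0.6188) = 29.5%, +2.3 points.

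A completeness gap of about one point is enough to reach the margin. In the last case about 2.63 million of the expected 3 million patients are retained (3 million × 0.8772), so loss of numbers is not the issue.

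**The case against.** The strongest reply is that this is a wording slip in a descriptive, hypothesis-generating study, with no demonstrated effect on any result. Much of that stands.

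- A reader might infer that the first-paragraph rule is shown to select sicker people and to overstate multimorbidity. The documents do not support this. Section J says only that hospital data raise ethnicity completeness. It gives no figure and does not say that people lacking ethnicity are healthier. Selection on hospital use is a risk whose size may be zero.
- A reader might see an equal conflict over deprivation. Section J counts both patient-level and practice-level IMD as linked measures, so the first-paragraph condition can be read to include the practice-level proxy and would then exclude few people or none. The hospital mechanism does not apply to deprivation. A clarification is enough.
- A reader might infer that the contradiction biases comparisons between ethnic groups. Those comparisons need recorded ethnicity under either rule, so they use the same people.
- The 0.2-point margin and the 27.2% come from a prevalence calculation based on a study of 36 conditions. The primary outcomes are clusters and trajectories over 220 conditions. Nothing here quantifies an effect on clusters.
- The population described in Section N as unselected is already limited by Section K to acceptable, linkage-eligible patients with a recorded condition, and Section T acknowledges related selection. The phrase may mean no more than not selected by ethnicity.

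The contradiction itself survives all of this. It is not a detail left for a later analysis plan, because the protocol states both rules. Existing restrictions on the population are no reason to add one that the overall clustering does not need.

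**Conclusion.** Section P contradicts itself on people with missing ethnicity, and no other section resolves it. As written, the population for the overall prevalence and clustering, and so for a primary outcome, depends on which paragraph is followed. That much rests on the text alone and needs no assumption.

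The consequence cannot be sized from the protocol. The bias in overall prevalence is zero if people lacking ethnicity have the same prevalence as the rest. It passes the plan's 0.2-point margin once their prevalence is lower by more than about 1.8 points with 10% missing, or 0.8 points with 20% missing. Both missing fractions are assumed. The upward direction is plausible from Section J but not established. The point concerns the overall analyses only.

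**What to change.** Replace the inclusion rule in the first paragraph of Section P with one rule per analysis.

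- Overall prevalence and clustering (not stratified by ethnicity): include everyone with known age and sex, whether or not ethnicity is recorded.
- Ethnicity-stratified prevalence and clustering: require recorded ethnicity. Say which analyses these are, so that Sections O and P name the same stratifiers.
- Deprivation: state that linked measures include the practice-level IMD proxy of Section J.
- Sensitivity analysis: repeat the overall analyses in people with recorded ethnicity.
- Reporting: tabulate ethnicity completeness by age, sex and any hospital admission, so that readers can judge the selection risk from data.

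The cost is a few lines of protocol wording, one extra analysis and one completeness table. No new data are needed. The change should be made before the analysis population is built.

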### Q. Patient or user group involvement

The proposed research is supported by the Public Patient Involvement (PPI) strategy that underpins the MRC and NIHR awards funding it. Across these studies, we have gained support of existing PPI groups in the prioritisation of our research and they have supported the need an approach being taken. It is worth noting that most PPI groups are predominantly single disease-focused and therefore multimorbidity is a new area for them. Our ongoing PPI strategy

[figure not shown]

across both of these grants will engage the public and patients throughout the research pathway, now from the conduct to dissemination of our findings. We will also receive support from the North Thames Applied Research Collaborative (ARC) with PPI activities.

